### 2.9. Statistical analysis plan

Data will be analysed following the intention-to-treat principle. Missing data will be addressed using multiple imputation techniques [48]. Data will be stored and processed using Microsoft Excel, SPSS 28.0, and NVivo 20 Pro. No serious negative outcomes are anticipated for participants; therefore, an interim analysis will not be conducted and no formal stopping rules have been established.

#### 2.9.1. Participant characteristics analysis.

Participants’ characteristics will be summarised using descriptive statistics. Means, standard deviations (SDs), medians, and interquartile ranges will be reported for continuous variables. Frequencies and percentages will be reported for categorical variables.

#### 2.9.2. Primary outcomes analysis.

Primary outcomes will be analysed using descriptively, using the same approach for descriptive statistics outlined above. Specifically,

**Feasibility** outcomes will be analysed using counts and percentages, along with participants’ responses to survey questions. Recruitment efficiency will be deemed feasible if 80% of the recruitment target is met in terms of participants randomised. Retention will be considered successful if 70% of participants stay in the intervention. Adherence will be regarded as successful if 50% of participants spend at least 75% of the recommended time on the platform. Technical feasibility will be deemed successful if 80% of participants report no significant technical issues, defined as problems that prevent or severely hinder access or completion (e.g., frequent login failures or content not loading). Data collection efficacy will be considered successful if 90% of all required assessments are completed.**Acceptability** outcomes will be analysed using counts and percentages, along with participants’ responses to survey questions and a qualitative thematic analysis of open-ended responses. Participation rates will be deemed acceptable if they exceed 70% in each of the units and assigned activities. Participation burden will be considered acceptable if 75% of participants report that the effort required to engage with the programme is reasonable. Participants’ perspectives on the intervention will be assessed based on themes identified from their feedback on the open-ended survey questions. General acceptability will be regarded as successful if 75% of participants rate the programme as satisfactory or higher.

#### 2.9.3. Secondary outcomes analysis.

Critical thinking ability, decision-making skills and eHealth literacy will be analysed using survey scores, comparing mean changes at end of intervention between intervention and control group. Knowledge application and intended behaviours and self-efficacy will be assessed through survey responses.

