**Discussion:**

This pilot trial will inform the design and conduct of a future definitive randomised trial. Insights gained will inform sample size estimations, refine recruitment strategies, optimise programme delivery, and improve data collection processes, ensuring a robust and scalable approach for the definitive trial.

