### 2.4. Sample size

Following guidance for pilot trials [37–40], we will recruit 30 participants per group to allow for an anticipated 15%−25% attrition rate [32]. This target will provide sufficient numbers (20–25 participants per group) for assessing feasibility outcomes including recruitment, retention, and adherence rates [41–45].

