### 2.5. Randomisation

After informed consent and baseline data collection, participants will be randomised to study arms using stratified randomisation based on cancer experience (current patients, survivors, informal caregivers, and loved ones) to ensure balanced representation across these groups. Participants will be randomly assigned in a 1:1 ratio to either the IHC-C intervention group or the waitlist control group through the QuestionPro survey platform [46]. To implement stratified randomisation, separate block paths will be configured in the platform’s survey logic for each stratum, with each stratum identified based on participants’ responses to a question about their cancer experience. Within each stratum-specific block, the platform’s automated block randomisation feature will be used, with the “evenly present blocks” setting enabled to maintain balance between groups to make sure the randomisation occurs independently within each stratum, consistent with standard stratified randomisation procedures, and reduces the risk of allocation imbalances that can occur in small-sample pilot trials. Allocation will remain concealed from researchers throughout the process.

Based on earlier recruitment for this programme, we anticipate a higher proportion of survivor respondents [32]. To avoid excluding these volunteers while still preventing extreme imbalance, we will not impose fixed numeric quotas per stratum. Instead, stratified randomisation will continue until the overall sample reaches N = 60. If any stratum remains under-represented (≤ 10 participants) when total enrolment nears 50, targeted advertising will be used to bolster that subgroup.

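### Section 2.9.3 compares mean changes between arms; if baseline scores exist, adjusting T1 scores for baseline and stratum is usually more precise and gives better planning figures

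*Protocol article*

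**What the plan says.** Section 2.9.3 sets the analysis of the scored secondary outcomes: "Critical thinking ability, decision-making skills and eHealth literacy will be analysed using survey scores, comparing mean changes at end of intervention", the contrast being intervention against control. It names no model, test or covariate.

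Section 2.5 describes "stratified randomisation based on cancer experience (current patients, survivors, informal caregivers, and loved ones" as the allocation scheme, with 1:1 allocation. In the analysis sections, that four-level factor returns only in Section 2.9.4, for optional descriptive subgroups.

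On whether a baseline score exists, the text points two ways. Section 2.9.3 needs one, because a change cannot be formed without it. Section 2.8.3 places both the critical-thinking tool and eHEALS after the intervention and mentions no baseline administration. Section 2.8.4 has all participants complete baseline assessments but does not name the instruments. Fig 1, which may settle this, is not shown.

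On purpose, the abstract says of the pilot as a whole: "Insights gained will inform sample size estimations". It names no SD, outcome or formula. Section 2.4 justifies the pilot's own size as "sufficient numbers (20–25 participants per group) for assessing feasibility outcomes", not for the secondary scores.

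**The concern.** A difference in mean change subtracts the whole baseline score from each follow-up score. When the two scores correlate only moderately, this adds baseline noise to the contrast. Regressing the follow-up score on baseline removes only as much of the baseline as predicts follow-up. In small arms it also deals better with chance baseline imbalance, which a change score over-corrects through regression to the mean.

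Two things are at stake. The first is the width of the interval around the preliminary between-arm difference. The second is the planning information that the pilot yields. A summary of changes alone gives the SD of change. It does not give the baseline-to-T1 correlation or the adjusted residual SD, and a definitive trial analysed with baseline adjustment would need those. Separately, an analysis after stratified randomisation should normally reflect the strata, and this sentence does not.

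**Working it through.** **Inputs from the protocol article.** 30 per group, 60 in total, 15% to 25% attrition, 20–25 evaluable per group (Section 2.4); 1:1 allocation and four strata (Section 2.5); between-arm comparison of mean changes (Section 2.9.3). The article gives no SD, correlation, effect size, alpha or power for these outcomes. Every rho below is therefore an assumption, shown as a range.

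**The plan's own figure.** 2 × 30 = 60. 30 × 0.85 = 25.5 and 30 × 0.75 = 22.5, so about 22 to 25 evaluable per group. The upper end matches the stated 25. The stated 20 would need 33% attrition. I use 22 per arm below.

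**Precision in general.** Let s0 and s1 be the SDs at baseline and T1, and rho their correlation.

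- Variance of change: s0² + s1² − 2·rho·s0·s1
- Residual variance after baseline adjustment: s1²(1 − rho²)
- Difference between them: (s0 − rho·s1)²

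The difference is never negative, but it is zero when rho = s0/s1, which can happen below 1. With equal SDs (s0 = s1 = s) the two variances are 2s²(1 − rho) and s²(1 − rho²), and their ratio is (1 + rho)/2.

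| Assumed rho | Change variance (s = 1) | Adjusted variance | Ratio (1 + rho)/2 | Inverse |
|---|---|---|---|---|
| 0.3 | 1.40 | 0.91 | 0.65 | 1.54 |
| 0.5 | 1.00 | 0.75 | 0.75 | 1.33 |
| 0.7 | 0.60 | 0.51 | 0.85 | 1.18 |
| 0.9 | 0.20 | 0.19 | 0.95 | 1.05 |

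The T1 score alone has variance 1.00. Below rho = 0.5 the change score is therefore less precise than ignoring baseline altogether.

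**At the pilot's size.** These are SEs of the between-arm difference in SD units at 22 per arm. The simulated columns come from data with four strata exactly balanced by arm. The last two columns use a large-sample formula; the second of them adds a small-sample penalty for four covariate terms whose balance is left to chance.

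| Assumed rho | Change, simulated | Baseline-adjusted, simulated | Change, formula | Baseline plus stratum, formula |
|---|---|---|---|---|
| 0.3 | 0.361 | 0.292 | 0.357 | 0.303 |
| 0.5 | 0.302 | 0.269 | 0.302 | 0.275 |
| 0.7 | 0.232 | 0.217 | 0.234 | 0.227 |
| 0.9 | 0.133 | 0.132 | 0.135 | 0.138 |

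The simulated SE falls by 19% at rho 0.3 (0.292/0.361 = 0.81), 11% at 0.5, 6% at 0.7 and 1% at 0.9. Under the less favourable formula the gains are 15%, 9% and 3%, with a loss of about 2% at 0.9. Stratified allocation keeps the strata close to balanced before attrition, so the truth should lie nearer the simulated column.

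**The stratum term.** A stable difference in score level between strata appears at both times and cancels in a change score. In the simulation, adding the four-level stratum to the baseline-adjusted model changed the SE by at most 0.001, including with an assumed between-stratum SD of about 0.5.

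**Sizing illustration.** Assume a difference of 0.5 SD, 90% power and two-sided 5%. Then n per arm = 2(1.960 + 1.282)² × variance / 0.5², which is about 84.1 × variance, rounded up. Sized for change against sized for the adjusted analysis, this gives 118 against 77 at rho 0.3, 85 against 64 at 0.5, 51 against 43 at 0.7, and 17 against 16 at 0.9. Each number is correct for its own analysis. An excess arises only if the first is used for a trial analysed the second way.

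**The case against.** The strongest reply is that the article is condensed and its silence on covariates proves little. A comparison of mean changes can itself be baseline-adjusted: regressing change on arm and baseline gives the same arm coefficient as regressing T1 on arm and baseline. Covariate lists are commonly left to a fuller plan. This stands in part. The omission of a stratum term alone would not justify a point. But the sentence does name a contrast, and as it reads that contrast is a difference in mean change.

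A second reply is that the baseline score may not exist. This stands as a condition. Without a baseline, neither the stated mean change nor the baseline adjustment is possible, so Section 2.9.3 would need rewording in that case too.

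A third is that these are secondary outcomes of a feasibility pilot, and that a between-arm comparison of change is valid under randomisation. This stands in full: the matter is efficiency and planning information, not bias.

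A reader might also infer three stronger claims that the document does not support:

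- **The definitive trial will be oversized.** That needs the change-score SD to be used to size a trial that is then analysed with baseline adjustment. The article states neither step. Its abstract speaks only of informing sample size in general.
- **Leaving out the stratum inflates the error appreciably.** Stable level differences cancel in change, and nothing in the article says that strata differ in how much they change.
- **Change is less precise at every correlation below 1.** That holds only when the SDs are equal at the two times.

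**Conclusion.** The point holds as an efficiency improvement to a secondary analysis. With baseline scores available and similar SDs at both times, baseline adjustment cuts the variance to 0.65, 0.75, 0.85 or 0.95 of the change-score variance at assumed rho of 0.3, 0.5, 0.7 or 0.9. At 22 per arm the gain is material at low to moderate correlation and negligible near 0.9. The article does not give rho, so the range is the answer.

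The stratum term belongs in the model because the randomisation used it; little extra precision should be expected once baseline is included. No stated figure, feasibility threshold or primary conclusion is affected. The effect is confined to the precision of the secondary contrasts and to what the pilot can pass on to the definitive trial. Whether a baseline score is collected must be settled first.

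**What to change.** 1. Reconcile Sections 2.8.3, 2.8.4 and 2.9.3: state for each scored instrument whether it is given at baseline as well as at T1.
2. In Section 2.9.3, replace the comparison of mean changes with a linear regression of T1 score on arm, baseline score and the four-level cancer-experience stratum. Report the adjusted between-arm difference with a 95% CI.
3. If an instrument has no baseline, compare T1 scores adjusted for stratum, and drop the reference to change.
4. Report the SD at baseline and at T1, the residual SD and the baseline-to-T1 correlation, so that the definitive trial can be sized for whichever analysis it adopts.

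The cost is a few sentences. No data are needed beyond the baseline scores that mean change already requires, and the SPSS software named in Section 2.9 fits the model. Baseline and stratum add four parameters to a plain two-arm comparison. With 45 to 51 participants (60 × 0.75 and 60 × 0.85) and six parameters in all, 39 to 45 residual degrees of freedom remain.

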#### 2.7.3. Waitlist control group.

Participants assigned to the waitlist control group will gain access to the IHC-C programme after four weeks, once the intervention group completes the programme and assessments. Participants in the waitlist group will then have four weeks to complete the programme, during which they will receive the same support, reminders, and resources as those in the intervention group. All data collection, including baseline and follow-up assessments, will be conducted using the same tools and methods to ensure comparability of outcomes across both groups. As the primary aim of this pilot study is to inform the design of a future definitive trial, this waitlist control design allows for a controlled comparison of feasibility and acceptability between groups during the intervention phase, while ensuring that all participants ultimately receive access to the programme.

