#### 2.8.3. Secondary outcomes.

This pilot trial will also collect outcomes intended for the future definitive trial, focusing on:

Critical thinking and decision-making skills involve participants’ ability to appraise evidence, identify misleading claims, and assess the reliability of health information, enabling them to make well-informed decisions learned from the intervention. Data will be collected post-intervention using the structured evaluation tool *Critical Thinking in Cancer and Health Information Evaluation: Scenario-Based Assessment, which includes* four scenarios with 17 questions developed specifically for the IHC-C programme.eHealth literacy: participant’s experience using the internet for health information, measured with the 8-item eHealth Literacy Scale (eHEALS) [47] post-intervention.Cognition and behaviour change: participants’ self-reported changes in understanding and approach to engaging with information. Data will be collected through two specific questions.

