#### 2.8.4. Assessment timeline.

Assessments will occur at four time points (see Fig 1):

T − 1 (Baseline assessment): All participants will complete baseline assessments.T0 (Allocation): Randomisation and assignment to the intervention or waitlist control group. No assessments are conducted at this timepoint.T1 (Post-intervention: 4 weeks): Both groups complete assessments – intervention group after completing the programme, control group without programme access.T2 (Control access: 6 weeks): Waitlist control group receives programme access.

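### The planned comparison of mean changes in critical thinking, decision-making and eHealth literacy is not supported by the stated timing of the two instruments, which is post-intervention

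*Protocol article*

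**What the plan says.** Section 2.9.3 fixes the analysis of the scored secondary outcomes as "comparing mean changes at end of intervention between intervention and control group".

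Section 2.8.3 fixes when those scores are obtained, separately for each instrument. For the 17-question scenario test, which covers critical thinking and decision-making: "Data will be collected post-intervention using the structured evaluation tool". For eHealth literacy: "measured with the 8-item eHealth Literacy Scale (eHEALS) [47] post-intervention". Neither entry mentions a baseline administration.

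Three other places refer to a baseline without listing its instruments:

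- Section 2.5: "After informed consent and baseline data collection, participants will be randomised to study arms".
- Section 2.8.4, T-1 entry: "All participants will complete baseline assessments". The T1 entry reads "T1 (Post-intervention: 4 weeks): Both groups complete assessments".
- Section 2.7.3: "All data collection, including baseline and follow-up assessments, will be conducted using the same tools and methods". The reason given there is comparability between the two groups.

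**The concern.** A mean change is a follow-up score minus a baseline score on the same scale. If the two instruments are given when section 2.8.3 says, the first term exists and the second does not. The multiple imputation planned in section 2.9 could not help, because a baseline that is absent for every participant leaves nothing to impute from.

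The abstract says that these measures will support the choice of key outcomes for the definitive trial and that the pilot will inform its sample size. Without baseline scores the pilot would give no change, no correlation between baseline and follow-up, and no view of whether participants already score near the ceiling before the programme. A pre-randomisation score cannot be collected once a participant has been allocated.

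**Working it through.** **Step 1. Set the sections side by side.** The point rests on no stated figure, so the main check is textual.

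| Question | Section | What the text gives |
|---|---|---|
| What is compared? | 2.9.3 | Mean changes between groups at end of intervention |
| When is the scenario test given? | 2.8.3 | Post-intervention |
| When is eHEALS given? | 2.8.3 | Post-intervention |
| Is there a baseline assessment? | 2.5, 2.6, 2.8.4 | Yes, before randomisation; instruments not named |
| Same tools at baseline and follow-up? | 2.7.3 | Same tools and methods; can mean across arms or across time points |
| Which instruments at which time point? | Fig 1, S2 File | Not visible here |

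The first three rows do not fit together. The next two leave room for a baseline score but do not state one. Section 2.8.1 describes a demographic and cancer survey, but does not say that this is the whole of the T-1 content, so it cannot be used to rule the instruments out.

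**Step 2. See whether the choice of reading matters.** Section 2.4 plans 30 per group ("we will recruit 30 participants per group to allow for an anticipated 15%−25% attrition rate") and expects 20 to 25 per group to remain. As a check, 30 × 0.85 = 25.5 and 30 × 0.75 = 22.5, so 20 lies a little below the range implied by the stated attrition. I use 20 and 25.

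Assume equal SDs at both time points and a baseline-to-T1 correlation ρ. The documents give no ρ; 0.3 to 0.7 is assumed. The 95% half-width of the between-group difference, in SD units, is:

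- T1 score alone: 1.96 × √(2/n)
- change score: 1.96 × √(4(1 − ρ)/n)
- T1 score adjusted for baseline: 1.96 × √(2(1 − ρ²)/n)

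| n per group | ρ | T1 alone | Change | Baseline-adjusted |
|---|---|---|---|---|
| 20 | 0.3 | 0.62 | 0.73 | 0.59 |
| 20 | 0.5 | 0.62 | 0.62 | 0.54 |
| 20 | 0.7 | 0.62 | 0.48 | 0.44 |
| 25 | 0.3 | 0.55 | 0.66 | 0.53 |
| 25 | 0.5 | 0.55 | 0.55 | 0.48 |
| 25 | 0.7 | 0.55 | 0.43 | 0.40 |

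The readings are different analyses with different precision. Below ρ = 0.5 the change score is less precise than the T1 score alone.

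**Step 3. Illustrate the consequence for the definitive trial.** Relative to comparing T1 scores, the required sample size is multiplied by 1 − ρ² with baseline adjustment (0.91, 0.75, 0.51 at ρ = 0.3, 0.5, 0.7) and by 2(1 − ρ) with change scores (1.4, 1.0, 0.6). The first set applies only if the definitive trial adjusts for baseline, which this protocol does not plan. The pilot would also estimate ρ loosely. With 45 completers (60 × 0.75) and an observed ρ of 0.5, Fisher's interval is tanh(0.549 ± 1.96/√42), about 0.24 to 0.69, so 1 − ρ² would run from about 0.94 to 0.52.

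**The case against.** The strongest reply is that baseline scores are probably intended. Section 2.9.3 itself plans a change, all participants have a baseline assessment, and section 2.7.3 speaks of the same tools at baseline and follow-up. The timing in section 2.8.3 may only mark the outcome time point, and Fig 1 may list both instruments at T-1. A figure that is not shown here is not a gap in the plan.

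Much of this stands. A reader might infer that the instruments are given at T1 and at no other time, so that no change score can be formed. The documents do not support that: section 2.8.3 does not exclude a baseline administration, and the T-1 content is unlisted rather than listed without these instruments. Nor does section 2.7.3 prove a contradiction, since its stated purpose suggests the same tools across arms.

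It is also fair that the stakes are limited. The abstract calls these measures preliminary, the primary outcomes are descriptive, and no success criterion in section 2.9.2 uses these scores. A reader might infer that the missing correlation would decide the size of the definitive trial; the wide interval in step 3 shows that a pilot of this size would settle little.

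What remains is that two stated rules do not fit. This is not a detail left to an unseen analysis plan: the article gives both the timing and the analysis, and no analysis plan can supply scores that were not collected.

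**Conclusion.** The point holds as an inconsistency to be reconciled. The text plans a change-score comparison for outcomes whose stated collection is post-intervention, and it does not say what the T-1 assessment contains. If Fig 1 places both instruments at T-1, section 2.8.3 needs correcting; if it does not, section 2.9.3 cannot be carried out as written. One of them must change in either case.

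It concerns both scored secondary outcomes in all 60 planned participants and should be fixed. Confidence is medium because the schedule is not visible. The precision and sample-size figures illustrate what depends on the choice under assumed correlations and equal SDs; they do not measure a loss that has been shown to occur.

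**What to change.** Reconcile sections 2.8.3, 2.8.4 and 2.9.3, and check them against Fig 1, in one of two ways, chosen separately for each instrument:

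1. **Baseline collected.** State in section 2.8.3 and in the T-1 entry of section 2.8.4 that the instrument is completed before randomisation and again at T1. In section 2.9.3, preferably compare T1 scores adjusted for the baseline score. At each ρ in the table this is more precise than either alternative.
2. **Baseline deliberately not collected**, for example to avoid a practice effect on the scenario test. Replace the mean-change comparison for that instrument with the between-group difference in T1 score.

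For anyone already randomised, the text should describe what was actually collected.

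If the instruments are already in the baseline survey, or if option 2 is taken, the cost is wording only. If they must be added, it is up to 8 + 17 = 25 further items at baseline. That adds burden in a trial where burden is an acceptability outcome, and more items to count towards the 90% assessment-completion criterion. It also brings a possible practice effect, or a pretest effect that interacts with the programme and so need not fall equally on both arms.
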